#### Randomization

Following completion of the behavioral survey, participants were randomized into either the intervention or the wait-list control group. Participants were successfully randomized within 18 strata based on the three serostatus/risk groups, three cities, and race/ethnicity (non-Hispanic white or not), ensuring balance in randomization for these three dimensions [27]. Within the strata of city, serostatus/risk group, and race/ethnicity, participants were randomly assigned to the next treatment allocation from a randomly permuted block sequence (block sizes were 2 and 4).

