### Data Analysis Plan

We will conduct bivariate analyses, stratified by intervention group, for characteristics related to demographic factors, educational history, social determinants of health, city of enrollment, risk group, and baseline behaviors, to assess for failure of randomization. Failure of randomization will be defined by a significant (*P*<.05) difference in the distribution of a characteristic between the intervention and control groups.

The primary outcomes of interest in this study (Table 2) will be associated with the following alternative hypotheses: assignment to the intervention group will be associated with increased HIV testing among HIV-negative men, increased engagement with HIV care and ART use/adherence among people living with HIV, increased uptake and adherence to PrEP among higher risk HIV-negative men, sustained lack of condomless anal sex among lower risk HIV-negative men, increased condom use for those who reported prior condomless sex, and increased STI testing for all sexually active men. Assuming that there are no failures of randomization, we will use descriptive analyses to calculate the ratios of rates or prevalence between participants assigned to the intervention group and participants assigned to the control group. For HIV testing, PrEP uptake, and STI testing, we will consider using descriptive methods for time-to-event analysis and describing unadjusted hazard ratios if randomization does not fail. If a failure of randomization occurs, we will conduct a stratified analysis for the association between outcomes and randomization assignment by variable where the failure occurred and will consider adjusting estimates for that factor if indicated.

**Table 2 table2:** Primary outcomes.

Outcome	Participant HIV risk group	
	Lower risk and higher risk HIV-negative	HIV-positive
HIV testing	✓	
Engagement in HIV preventative care	✓	
PrEP^a^ uptake	✓	
PrEP adherence	✓	
Engagement in HIV care		✓
ART^b^ uptake		✓
ART adherence		✓
Condom use	✓	✓
Condom use compliance	✓	✓
STI^c^ testing	✓	✓

^a^PrEP: pre-exposure prophylaxis.

^b^ART: antiretroviral therapy.

^c^STI: sexually transmitted infection.

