Our study is subject to a number of possible limitations, typical of the potential biases associated with randomized prevention trials [38]. It is possible that we might have selection bias, manifested as a failure of randomization. We have taken steps to mitigate this possibility by implementing stratified randomization by site and risk group; stratified randomization minimizes the risk for failure of randomization across a domain that might be associated with efficacy. We will assess failure of randomization by comparing the distribution of key participant characteristics by randomization arm, using chi-square or Fisher exact tests as appropriate. We anticipate that there could be measurement bias because we are relying on self-reported outcomes, as is common in behavioral studies. We have attempted to minimize this bias by allowing options for completing assessments privately or remotely, by using previously established or validated items, and by measuring key outcomes with multiple measures (for example, adherence is assessed in both 7-day and 30-day recall periods, and assesses condom use in the past 3 months and at last sexual encounter). We could be subject to exclusion bias if there is differential loss to follow-up between the intervention and control arms. We mitigated this risk by using proven approaches to increase retention in both arms, including multiple modes of contact (phone, email, text message) and offering flexible options for completing surveys at home or in the research clinic. Because we set quotas to ensure adequate representation of men of color and high- and low-risk HIV-negative men, our sample may not have high external generalizability; however, we have designed the study to have power to analyze within specific, high-priority groups of participants, given their importance in HIV epidemics among MSM living in the United States. Because of the recruitment structure, cross-sectional analyses of the levels of prevention and risk behaviors from the baseline data should be interpreted in light of the sampling strategy.

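### The default comparison is a crude ratio that leaves out the stratification factors and baseline behavior, so precision may be lost, by an amount the protocol does not let us determine

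*Protocol article*

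**What the plan says.** Randomization (Methods): "Participants were successfully randomized within 18 strata based on the three serostatus/risk groups, three cities, and race/ethnicity", in permuted blocks of 2 and 4.

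Data Analysis Plan: baseline characteristics, including city and risk group, are compared between arms. "Failure of randomization will be defined by a significant (*P*<.05) difference in the distribution of a characteristic" between the arms. If none is found, "we will use descriptive analyses to calculate the ratios of rates or prevalence between participants assigned to the intervention group" and the control group. For HIV testing, PrEP uptake and STI testing, the authors will also consider time-to-event methods, "describing unadjusted hazard ratios if randomization does not fail". If a failure is found, the association is examined in strata of the variable concerned, and the authors "will consider adjusting estimates for that factor if indicated".

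The unadjusted default and the condition for leaving it are therefore stated rules. They are not details left to an analysis plan that is not shown.

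**The concern.** Blocking within 18 strata forces the arms to be nearly equal on risk group, city and race/ethnicity. If these factors predict the outcome, the difference between arms varies less from trial to trial than the usual formula for a crude ratio assumes. That formula then reports too large a standard error. The precision gained at randomization is real, but the reported interval does not show it.

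Risk group is a plausible predictor, because the Methods Overview defines it by serostatus, recent condomless anal sex and PrEP use, which lie close to several primary outcomes. The baseline survey also recorded earlier testing, sexual behavior, PrEP use and ART use. The default comparison uses none of these as covariates.

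At stake is precision, not bias. Precision matters because the Discussion claims power to analyse specific high-priority groups, where numbers are smaller.

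**Working it through.** **Inputs from the protocol.** 1229 men enrolled: 478 + 335 + 416 = 1229. 1:1 allocation. 3 × 3 × 2 = 18 strata. Blocks of 2 and 4. No effect size, event rate or prognostic strength accompanies the target of at least 1200, so there is no planned power to reproduce. The share of outcome variance explained by the strata, R², is an **assumption** throughout.

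**Step 1: effect of ignoring the strata.** Under stratified allocation the true standard error is about k = √(1 − R²) times the crude one (linear approximation).
- Excess interval width = 1/k − 1.
- True level of a nominal 5% test = 2·[1 − Φ(1.96/k)].
- Take an effect of 2.80 crude standard errors (1.96 + 0.84), which nominally gives 80% power. Power of the crude test = Φ(0.84/k). Power of the strata-adjusted test = Φ(2.80/k − 1.96).

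| R² (assumed) | Interval too wide by | True level | Power, crude | Power, adjusted |
|---|---|---|---|---|
| 0.02 | 1.0% | 4.8% | 80.2% | 80.8% |
| 0.05 | 2.6% | 4.4% | 80.6% | 82.0% |
| 0.10 | 5.4% | 3.9% | 81.3% | 84.0% |
| 0.20 | 11.8% | 2.8% | 82.7% | 87.9% |

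For scale: with two equal groups centred on 50% prevalence, R² equals the squared gap between them. R² = 0.02 needs a gap of √0.02 = 14 points, 0.10 needs 32 points and 0.20 needs 45 points.

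**Step 2: simulation of the allocation.** N = 1229, 18 strata, blocks of 2 and 4, 3000 runs per scenario, control rate roughly 45–50%, true difference 0 or 8 points. Prognostic strength is assumed. Adjusted ratios were standardized from a linear regression in each arm. The Monte Carlo error of a 5% rejection rate is √(0.05 × 0.95/3000) = 0.4 points.

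| Prognosis | Crude SE, reported vs true (no effect) | Rejection under no effect: crude → strata | Power: crude → strata → strata + baseline |
|---|---|---|---|
| Weak | 0.0639 vs 0.0641 | 5.3% → 5.3% | 80.0 → 79.9 → 81.6% |
| Moderate | 0.0643 vs 0.0597 | 3.8% → 5.0% | 82.0 → 84.5 → 89.0% |
| Strong | 0.0639 vs 0.0552 | 2.2% → 5.1% | 82.5 → 89.5 → 96.1% |

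The implied R² for the strata is 1 − (0.0597/0.0643)² = 0.14 in the moderate case and 1 − (0.0552/0.0639)² = 0.25 in the strong case. The strong case lies beyond the range in Step 1 and is an outer bound.

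The two sources of gain differ in kind. Adjusting for the strata leaves the true spread of the estimate unchanged (0.0597 vs 0.0596, moderate) and corrects the reported standard error. Adding the baseline value lowers the true spread (0.0596 to 0.0563, moderate). So the crude interval is too wide with respect to the strata, but only less efficient with respect to the baseline value.

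**Step 3: can the imbalance rule repair this?** With blocks of at most 4, the arms differ by at most 2 men per stratum, so by at most 12 per city (6 strata each). The city chi-square among all enrolled men is then at most about 144/478 + 144/335 + 144/416 = 0.30 + 0.43 + 0.35 = 1.08, against a critical value of 5.99 on 2 degrees of freedom. City cannot trigger adjustment. Risk group and race/ethnicity are balanced by the same mechanism. Meanwhile, 20 independent characteristics (number assumed) tested at .05 give 1 − 0.95²⁰ = 64% chance of at least one failure. Adjustment would then follow chance imbalance, not prognostic value.

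**Step 4: where it applies.**
- *Pooled over risk groups:* HIV testing (HIV-negative men), STI testing and, per the abstract and Table 2, condom use in all men. All three strata factors vary in the all-men outcomes. For HIV testing, two risk groups are pooled.
- *Already restricted:* the hypotheses limit PrEP to higher risk men, sustained lack of condomless sex to lower risk men, increased condom use to men with prior condomless sex, and care and ART to men living with HIV. In a single risk group, only city and race/ethnicity remain.
- *Baseline measure:* HIV testing has a 3-month item at baseline and follow-up. STI testing has a 12-month baseline item against 3 months at follow-up.

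**The case against.** The strongest reply is that no loss is shown. The protocol gives no prognostic strength, and in the weak case nothing is lost. R² of 0.10 to 0.20 needs large gaps between strata. The plan names no variance formula, test or interval method, so a stratified variance around a marginal ratio is not excluded. Several outcomes are already restricted by risk group or baseline behavior. In men selected for prior condomless sex, for example, the baseline yes/no value is constant. The crude ratio is unbiased, and its test errs on the safe side.

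All of this stands as a limit on size and scope. It does not remove the point, because the protocol fixes an unadjusted default and ties adjustment to a test that the stratification factors are balanced by design to pass.

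Three stronger readings are not supported:
- *The crude analysis is biased or inflates false positives.* The direction is the opposite: tests are conservative when the strata matter.
- *A matching baseline value goes unused for every outcome.* Some baseline values are constant in the analysed group. Others, such as STI testing and engagement in care, have a different recall window.
- *The Discussion contradicts the design by citing* "implementing stratified randomization by site and risk group". It leaves out race/ethnicity, but it reads as shorthand for the full statement under Randomization and changes no analysis.

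**Conclusion.** The point holds as a recommendation on efficiency. If standard variance formulas are used and the strata are prognostic, crude intervals are somewhat too wide and tests somewhat conservative. The excess width runs from about 1% (R² 0.02) to about 12% (R² 0.20), and the true level of a nominal 5% test from about 4.8% to 2.8%. These R² values are assumptions, and the protocol cannot narrow the range. Leaving out the baseline value forgoes further precision of unknown size without making the crude interval invalid. The point is strongest for HIV testing, STI testing and condom use in all men. It is weaker for outcomes analysed within one risk group.

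**What to change.** Prespecify, for each primary comparison and whatever the imbalance tests show:
- a model such as modified Poisson (log link, robust variance) for prevalence ratios, or a stratified or adjusted Cox model for time-to-event outcomes;
- as terms, arm and the stratification factors that vary in the analysed group: city, race/ethnicity, and risk group where groups are pooled;
- in addition, the baseline measure of the outcome where it was collected and is not constant in that group: the 3-month item for HIV testing, and the 12-month item as a covariate (not an identical measure) for STI testing.

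The crude ratio can be reported alongside.

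The cost is a few lines of plan and slightly more modelling. Some of the 18 cells may be sparse, so main effects may be needed in place of all cells. A covariate-adjusted hazard ratio is conditional on the covariates and is not the same quantity as the crude one, so the plan should say which is primary.

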**Objective:**

The objective of the RCT was to test the efficacy of the Mobile Messaging for Men (M-Cubed, or M3) app among at least 1200 MSM in Atlanta, Detroit, and New York. The goal was to determine its ability to increase HIV testing (HIV-negative men), STI testing (all men), condom use for anal sex (all men), evaluation for PrEP eligibility, uptake of PrEP (higher risk HIV-negative men), engagement in HIV care (men living with HIV), and uptake of and adherence to antiretroviral medications (men living with HIV). A unique benefit of this approach is the HIV serostatus-inclusiveness of the intervention, which includes both HIV-negative and HIV-positive MSM.

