## Methods

### Overview

The Mobile Messaging for Men (M3) study was conducted in two phases. The first phase consisted of a series of focus groups and in-depth interviews to ensure that written messages, videos, and app features presented in the trial were appropriate for the audience. The second phase was an RCT, with MSM in three serostatus/risk groups randomized to receive either the intervention condition (M3 app) for a three-month exposure period or a waitlist-control condition with the option to receive the app for three months at the end of the study. The serostatus/risk groups were defined by self-report as: (1) HIV seropositive; (2) HIV seronegative at higher risk (condomless anal sex and not taking PrEP as prescribed in the past 3 months); and (3) HIV seronegative at lower risk (no condomless anal sex in the past 3 months, or condomless anal sex while taking PrEP as prescribed in the past 3 months). Postintervention data collection occurred at three time points: 3 months (immediately postintervention), 6 months (three-months postintervention), and 9 months (six-months postintervention) (see Figure 1). Participant follow-up will be completed in September 2019, with primary outcome analyses to follow. The study was reviewed and approved by the Emory University Institutional Review Board (Protocol #87684) and registered at ClinicalTrials.gov (NCT03666247).

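### Table 2 gives the primary PrEP outcomes to lower- and higher-risk HIV-negative men together, while the hypothesis (uptake and adherence) and the objective (uptake) limit them to higher-risk men

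*Protocol article*

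**What the plan says.** The protocol article describes the PrEP population in three places.

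- **Abstract, Objective:** "uptake of PrEP (higher risk HIV-negative men".
- **Data Analysis Plan, hypothesis:** "increased uptake and adherence to PrEP among higher risk HIV-negative men". The sentence ties itself to the table: "The primary outcomes of interest in this study (Table 2) will be associated with the following alternative hypotheses".
- **Data Analysis Plan, Table 2:** the only HIV-negative column is "Lower risk and higher risk HIV-negative", and both PrEP uptake and PrEP adherence are ticked in it.

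The Methods Overview defines the two groups. One is "HIV seronegative at higher risk (condomless anal sex and not taking PrEP as prescribed in the past 3 months". The lower-risk group is made up of men without recent condomless anal sex together with men reporting "condomless anal sex while taking PrEP as prescribed in the past 3 months".

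The planned effect measure is to "calculate the ratios of rates or prevalence between participants assigned to the intervention group" and those assigned to control. A second option is left open: "For HIV testing, PrEP uptake, and STI testing, we will consider using descriptive methods for time-to-event analysis".

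**The concern.** One primary outcome has two stated populations. The objective and the hypothesis agree with each other on uptake, and Table 2 differs from both. The difference is not neutral, because the group that Table 2 adds contains established PrEP users. They cannot start PrEP, yet they would count as having the outcome if uptake is analysed as the proportion on PrEP at follow-up.

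Two things are at stake. Either the pooled or the restricted result could be presented as the planned primary PrEP analysis once the data are seen. And the pooled result, under the prevalence reading, tests a different question from the stated hypothesis.

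The same mismatch affects PrEP adherence, with a further difficulty: the higher-risk group is defined at baseline by not taking PrEP as prescribed.

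**Working it through.** **Text comparison**

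| Place | PrEP uptake | PrEP adherence |
|---|---|---|
| Abstract, Objective | higher risk only | not named |
| Hypothesis, Data Analysis Plan | higher risk only | higher risk only |
| Table 2, Data Analysis Plan | lower and higher risk | lower and higher risk |

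The abstract's Methods paragraph says that risk-specific outcomes will be examined in subgroups where appropriate. It does not say which population is primary for PrEP.

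**Size of the effect on the result.** The article gives no PrEP rate, risk-group size or power for this outcome, so there is no figure to reproduce. From the document come only 1229 men and 1:1 allocation; everything else below is assumed.

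*Illustration A.* Three equal risk groups give 1229/6 = 204.8, taken as 204 men per arm per group. PrEP use in higher-risk men is 10% control and 20% intervention. Prevalent use in lower-risk men is 20%, 35% or 50% in both arms, that is, no effect there. The pooled proportion is the mean of the two groups. Power for two proportions at two-sided 5% is Φ(z), with

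z = [|p1 − p0| − 1.96·√(2·p̄(1 − p̄)/n)] / √([p0(1 − p0) + p1(1 − p1)]/n).

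| Population | n per arm | Control | Intervention | Ratio | Power |
|---|---|---|---|---|---|
| Higher risk only | 204 | 10% | 20% | 2.0 | 81% |
| Pooled, 20% on PrEP in lower risk | 408 | (10+20)/2 = 15% | (20+20)/2 = 20% | 1.33 | 47% |
| Pooled, 35% | 408 | (10+35)/2 = 22.5% | (20+35)/2 = 27.5% | 1.22 | 38% |
| Pooled, 50% | 408 | (10+50)/2 = 30% | (20+50)/2 = 35% | 1.17 | 33% |

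For the first row, z = (0.10 − 1.96 × 0.0354)/0.0350 = 0.88, which gives 81%.

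*Illustration B, separating prevalence of use from new starts.* Assume 80% of the 1229 are HIV-negative (983 men) and a share w of them is higher risk (0.35 to 0.65). In higher-risk men 10% against 18% are on PrEP at follow-up (ratio 1.80). A share q of lower-risk men is already on PrEP (0.2 to 0.6), 90% of whom continue in both arms. Lower-risk non-users start at 3% in both arms.

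- Prevalence of use in lower-risk men: L = 0.9q + 0.03(1 − q). At w = 0.5 and q = 0.4, L = 0.36 + 0.018 = 0.378.
- Pooled control: 0.5 × 0.10 + 0.5 × 0.378 = 0.239. Pooled intervention: 0.5 × 0.18 + 0.5 × 0.378 = 0.279. Ratio 1.17.
- New starts, existing users removed: the denominator is 0.5 + 0.5 × 0.6 = 0.8. Control: (0.05 + 0.3 × 0.03)/0.8 = 0.074. Intervention: (0.09 + 0.3 × 0.03)/0.8 = 0.124. Ratio 1.68.

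Over the whole grid the pooled prevalence ratio is 1.07 to 1.38, and the pooled new-start ratio is 1.55 to 1.75. If lower-risk non-users respond in the same proportion, the new-start ratio is 1.80, with no dilution.

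**The case against.** The strongest reply is that Table 2 is a coarse list by HIV status and the hypothesis sentence narrows it. That sentence also narrows the condom outcomes to men with or without prior condomless sex, and Table 2 does not split those either. On this reading the population is named, and only the table is loose. Part of this stands: the intended population is probably higher-risk men. But Table 2 labels its columns by risk group and explicitly names lower-risk men for the PrEP outcomes, so a reader following the table would be following the plan.

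The second reply concerns dilution. A reader might infer that pooling necessarily weakens the PrEP result. The documents do not support that:

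- Time-to-event methods are under consideration for PrEP uptake, and existing users would not be at risk of starting. The article does not commit to these methods, so the prevalence reading is possible but not established.
- A zero effect in lower-risk men is an assumption. Table 1 gives core PrEP messages to every group, risk status was updated during app use, and the Message Development Process section describes the additional PrEP messages as going to HIV-negative men with recent condomless sex, without excepting PrEP users.
- With no existing users and an equal proportional response, pooling would raise power (0.81 against 0.73 in Illustration B at w = 0.5).

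Third, the 81% in Illustration A uses all 204 higher-risk men per arm. Some may be on PrEP but not as prescribed; excluding them from an analysis of new starts would reduce that number. This stands.

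**Conclusion.** The contradiction holds and does not depend on any calculation: Table 2 and the hypothesis it is tied to name different populations for two primary outcomes, and the objective sides with the hypothesis on uptake.

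The consequence is conditional. If uptake is analysed as prevalence of use over the Table 2 population, and the effect in lower-risk men is small, the ratio is pulled toward 1. On the assumed inputs a ratio of 2.0 falls to between 1.33 and 1.17, with power falling from 81% to between 47% and 33%. If uptake means new starts among non-users, most of the dilution goes. These figures show direction and possible size; they are not estimates for this trial, and it should not be read as having lost that power.

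**What to change.** Before the arms are compared on PrEP outcomes:

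1. Split the HIV-negative column of Table 2 into lower and higher risk. Make higher-risk men the primary population for PrEP uptake, matching the objective and the hypothesis.
2. Define the population by the baseline randomization stratum, not by the risk status updated during app use.
3. Count uptake as new starts among men not on PrEP at baseline.
4. Report lower-risk men, excluding baseline PrEP users, only as a separate secondary analysis.
5. State the PrEP adherence population separately. Since higher-risk men were by definition not taking PrEP as prescribed at baseline, say whether adherence is assessed over the whole stratum or only among men on PrEP at follow-up, a group partly formed after randomization.

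The cost is one table and a few sentences. The stratum was used for randomization and current PrEP use is asked of HIV-negative men in the surveys, so no new data are needed. The small downside is fewer men in the primary PrEP comparison.
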